### Statistical analysis

Analysis will be performed on intention-to-treat basis.

Data will be checked for normal distribution using Kolmogorov-Smirnov test and presented as mean and standard deviation or as median and interquartile range as appropriate.

The primary end point is the difference of postoperative complication rate between the two group of patients. It will be evaluated using Fisher’s exact test or Pearson’s Chi square test as appropriate. Non-inferiority of experimental protocol respect to control group will be confirmed if the difference (including 95% confidence interval) will be lower than non-inferiority margin established at 10%. The 10% margin was chosen because it represents a two-thirds proportion of lower expected beneficial effect of PGDT (considering higher 95%CI for RR of 0.85) to reduce postoperative complications in comparison with conventional fluid therapy (RR 0.76 [CI95% 0.68–0.85]) [17].

Student t test or Mann–Whitney U test will be used to analyzed secondary outcomes as appropriate. Mortality between groups will be analyzed using the Kaplan-Meier method. The Log Rank test will be used to evaluate the statistical significance. Cox regression model using forward selection method for entering explanatory variables will be used to perform multivariate analysis. The age, type of surgery, ASA-PS classification and comorbidities will be considered as variables. A *p* value of F-test < 0.05 will be considered for variable inclusion. The amount of multicollinearity in the model will be estimated by the variance inflation factor (VIF). A VIF higher than 4 will be considered a sign of multicollinearity. Predicted R^2^ will be used to assess overfitting.

An interim analysis will be performed by independent statistician when 50% of information will be available (100 patients recruited). To monitor for harm or futility, the one-sided *p* value is calculated for testing the hypothesis HR = 1 versus the alternative HR > 1 (meaning the experimental treatment is doing worse than the standard treatment). If the *p* value is < 0.0394 at a monitoring time, then the trial would stop with the conclusion that non-inferiority cannot be claimed [18, 19]. Stopping rule for efficacy has not been defined [20].

For each statistical test, a *p* value < 0.05 is considered statistically significant.

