### Objectives

The primary objective is to evaluate the difference in developing overall complications during hospital stay between the two group of patients managed with two GDT protocols using a non-inferiority approach.

The secondary outcomes are the difference between the total amount of fluid administered, the total fluid balance, the needs of vasopressor/inotropes, the hospital length of stay and the mortality at day 28.

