### Sample size calculation

From literature analysis, we estimate a complication rate for control and experimental group of 28 and 35% respectively [2, 15]. With a non-inferiority margin of 10%, 184 patients (92 for each group) are needed to have a power of 80% and an alfa error of 0.05 [16]. Considering a 10% losing in follow-up, we enroll 200 patients (100 for each group).

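### The primary comparison names a test of zero difference with no stated role beside the valid confidence-interval rule, and leaves the named baseline variables unused

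*Protocol article*

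**What the plan says.** The Objectives section of the protocol article sets the primary comparison of complications "between the two group of patients managed with two GDT protocols using a non-inferiority approach". For that endpoint the Statistical analysis section gives two statements, one after the other.

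- A test: "It will be evaluated using Fisher’s exact test or Pearson’s Chi square test as appropriate".
- A decision rule: non-inferiority "will be confirmed if the difference (including 95% confidence interval) will be lower than non-inferiority margin established at 10"%.

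The section closes by setting 0.05 as the significance threshold for every test. It does not say what the Fisher or chi-square p value is for once the interval rule has been applied.

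Baseline variables appear in the same section, in a Cox model described directly after the mortality analysis: "The age, type of surgery, ASA-PS classification and comorbidities will be considered as variables". None is named for the complication endpoint. The Randomization section gives 1:1 allocation in blocks of 6 and states no stratification factor.

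**The concern.** As ordinarily applied, Fisher's and Pearson's tests have a null hypothesis of zero difference. Their p values make no reference to a margin, and neither test supplies the interval on which the decision depends. They are nevertheless the only tests named for a non-inferiority endpoint, and the general 0.05 threshold applies to them. A report could then lead with a non-significant p value that readers take as evidence of non-inferiority.

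The second matter is precision. The Inclusion criteria admit four kinds of surgery and ASA-PS classes II to IV, so risk of complications probably varies between patients. Age, ASA-PS class and type of surgery are known before surgery and already named in the plan, but the primary comparison does not use them.

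**Working it through.** **Inputs.** From the Sample size calculation section: "we estimate a complication rate for control and experimental group of 28 and 35% respectively"; then "With a non-inferiority margin of 10%, 184 patients (92 for each group) are needed to have a power of 80% and an alfa error of" (the alpha given there is 0.05, with sidedness not stated). From the Statistical analysis section: a 95% interval against a margin of 10%, read here as 10 absolute points. The difference is experimental (O2ERe) minus control (dynamic parameters), so a positive value is unfavourable to O2ERe.

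**1. The plan's own figure.** n per arm = [pc(1-pc) + pe(1-pe)] x (z_alpha + z_power)^2 / distance^2. The variance term is 0.28 x 0.72 + 0.35 x 0.65 = 0.4291. With one-sided alpha 0.05 and power 80%, (1.645 + 0.842)^2 is about 6.18. With distance 0.10 + 0.07 = 0.17, n = 0.4291 x 6.18 / 0.0289, which rounds up to 92. The stated size therefore reproduces only if the 7-point difference favours the experimental arm, the reverse of the labels.

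**2. One worked result.** Take control 26/92 and experimental 32/92.

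- Difference 0.0652, standard error 0.0683.
- 95% interval 0.0652 ± 1.96 x 0.0683, that is -6.9 to +19.9 points.
- Pooled z = 0.95, chi-square p = 0.34.

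The equality test is non-significant. Under the plan's interval rule non-inferiority is not shown, which is the correct conclusion.

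**3. How often the two statements differ.** Exact binomial enumeration at 92 per arm, with Pearson's test without continuity correction and a Wald 95% interval:

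| True rates, control / experimental | Chi-square non-significant | Interval rule met | Non-significant and non-inferiority not shown |
|---|---|---|---|
| 28% / 38% (at the margin) | 69.4% | 2.5% | 66.9% |
| 28% / 35% (as labelled) | 82.3% | 6.5% | 75.9% |
| 28% / 28% | 94.9% | 33.3% | 64.1% |
| 35% / 28% (labels reversed) | 82.3% | 70.3% | 29.6% |

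The first row gives the size of the possible misreading. The interval rule itself keeps its one-sided error near 0.025.

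**4. What adjustment could add.** Let r be the share of outcome variance explained by the covariates. The documents give no value, so 5%, 10% and 20% are assumptions. Approximate power under the 95% interval rule = Phi[(0.10 - (pe - pc)) / (SE x sqrt(1 - r)) - 1.96].

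- Equal rates of 28%: SE = sqrt(0.4032/92) = 0.0662. Power is 32.7% at r = 0, then 34.1%, 35.7% and 39.3%.
- Control 35%, experimental 28%: SE = sqrt(0.4291/92) = 0.0683. Power is 70.2% at r = 0, then 72.4%, 74.7% and 79.5%.
- Rates as labelled (control 28%, experimental 35%): 6.4% at r = 0, then 6.6%, 6.7% and 7.1%.

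The second case starts at 70% rather than 80% because 92 per arm matches one-sided 0.05, while a two-sided 95% interval corresponds to one-sided 0.025.

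**The case against.** The strongest reply is that the plan already contains the right decision rule. The sentence after the test names the difference, the interval and the margin, and ties non-inferiority to these alone. A reader might infer from the Fisher or chi-square sentence that an equality test decides non-inferiority, or competes with the interval as a second criterion. The documents do not support that: no sentence lets a p value settle the question, and the worked example comes out correctly under the written rule. This part of the objection stands. What remains is that a test unable to address the objective is named with no stated purpose.

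A reader might also infer that leaving out covariates is an error. It is not. An unadjusted risk difference is valid in a randomised trial, no stratification factor is stated that would call for adjustment, and listing variables for a Cox model creates no duty to use them elsewhere. The interval method and any adjustment model may properly sit in an analysis plan that is not shown. Their absence is not a finding, and adjustment is offered here only as an improvement.

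Finally, the 70% to 79% range should not be read as the trial's expected gain. It uses rates opposite to those the plan assigns to the arms. The shortfall in power is a separate sample-size matter and does not come from the choice of test.

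**Conclusion.** The point holds in a limited form. The conclusion on non-inferiority rests on a valid interval rule, and no failure of error control has been shown. The defect is one of role and wording: an equality test is attached to the primary endpoint without a purpose. Taken by itself as evidence of non-inferiority, its non-significance would accept a protocol worse by the full 10 points in about 69% of trials, against 2.5% under the interval rule. Those figures assume 92 analysed per arm, a 28% control rate and a Wald interval.

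Using the named baseline variables would improve the analysis without correcting any error. The gain is about 1 to 7 percentage points of power at equal rates of 28% (from 32.7% to 34.1-39.3%), and about 2 to 9 points with control 35% and experimental 28%. With the rates as labelled it is under 1 point. All of this depends on the assumed 5% to 20% of variance explained.

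**What to change.** In the Statistical analysis section, or in the analysis plan before outcome data are examined:

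- Make the risk difference in overall complications, O2ERe minus dynamic parameters, with its 95% confidence interval, the sole primary analysis. Obtain it by standardisation from a logistic model with treatment, age, ASA-PS class and type of surgery fixed in advance, without data-driven selection.
- Conclude non-inferiority only if the upper limit is below the margin.
- Report an unadjusted score-type interval, such as Newcombe or Miettinen-Nurminen, as a sensitivity analysis.
- Use any test of zero difference only for superiority, after non-inferiority has been shown.

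The cost is a change of wording, modest programming and a model to prespecify. No new data are needed. The model should stay small: the planning rates imply about 0.28 x 92 + 0.35 x 92 = 58 events. One term for treatment, one for age, two for ASA-PS class and three for type of surgery make seven, or about 8 events per term. Rules for merging sparse categories should therefore be set in advance.

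### The 10-point margin is justified as two-thirds of the conservative PGDT effect, but that 10% is a relative reduction; in absolute points the rule gives about 3 to 4

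*Protocol article*

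**What the plan says.** Four statements in the Protocol article bear on the margin.

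- **Endpoint scale** (Statistical analysis): "The primary end point is the difference of postoperative complication rate between the two group of patients". This is a difference between two proportions.
- **Decision rule** (same section): non-inferiority "will be confirmed if the difference (including 95% confidence interval) will be lower than non-inferiority margin established at 10" percent. The confidence bound for that difference is compared with 10 points.
- **Derivation** (same section): the margin was chosen because "it represents a two-thirds proportion of lower expected beneficial effect of PGDT (considering higher 95%CI for RR of 0.85"). The source effect is PGDT "in comparison with conventional fluid therapy (RR 0.76 [CI95% 0.68–0.85"]).
- **Sample size** (Sample size calculation): "we estimate a complication rate for control and experimental group of 28 and 35% respectively", and, with the same 10% margin, "184 patients (92 for each group) are needed to have a power of 80% and an alfa error of 0.05".

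No complication rate under conventional fluid therapy is given, and the relative effect is nowhere converted to percentage points.

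**The concern.** The derivation is on the risk-ratio scale and the decision is on the risk-difference scale. The two agree only if the baseline rate is 100%. At any realistic rate, 10 points is much more than two-thirds of the effect it is said to come from, and it may exceed that effect altogether.

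This margin decides the primary conclusion. Study design and setting supports a non-inferiority trial partly by expecting the PGDT effect to persist in both groups, and the Discussion regards a small difference between the protocols as acceptable. A reader told that 10 points is two-thirds of the conservative effect will take a positive result to mean that at least a third of that effect has been kept. The numbers do not support that inference.

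**Working it through.** **Inputs.** RR 0.76 with 95% CI 0.68–0.85, margin 10%, and the 95% CI rule come from Statistical analysis. Rates of 28% and 35%, 92 per group, 80% power and alpha 0.05 come from Sample size calculation. Which rate belongs to the control arm affects the result, so both are carried through.

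**1. Reproduce the stated margin.** 2/3 × (1 − 0.85) = 2/3 × 0.15 = 0.10. The stated 10% is obtained, as a relative reduction.

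**2. Confirm the scale on which it is used.** The endpoint and the decision rule both refer to a difference in rates, which settles the matter. The sample size agrees:

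n per group = (1.645 + 0.842)² × (0.35×0.65 + 0.28×0.72) / (0.07 + 0.10)² = 91.8, rounded up to 92.

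This match needs three things together: a 10-point absolute margin, the two rates exchanged relative to their labels (control 35%, experimental 28%), and one-sided alpha 0.05. With the rates as labelled, the same formula gives 2,948 per group. With the rates exchanged and 10% read as relative (3.5 or 2.8 points), it gives 241 or 277. The reproduction is therefore supporting evidence and not the main proof.

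**3. Convert the conservative effect to points.** With p the rate under control PGDT, the conventional-care rate is p/RR and the benefit is p/RR − p.

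| Control PGDT rate | Conventional rate at RR 0.85 | Whole benefit | Two-thirds of it | 10 points ÷ whole benefit |
|---|---|---|---|---|
| 28% | 0.28/0.85 = 32.9% | 4.9 points | 3.3 points | 2.0 |
| 35% | 0.35/0.85 = 41.2% | 6.2 points | 4.1 points | 1.6 |

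If 28% and 35% are instead conventional-care rates, the benefit is 0.28×0.15 = 4.2 or 0.35×0.15 = 5.25 points, and two-thirds is 2.8 or 3.5 points.

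For 10 points to be two-thirds of the benefit at RR 0.85, the conventional-care rate would have to be 0.15/0.15 = 100%.

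**4. Repeat at the point estimate.** At RR 0.76: 0.28/0.76 − 0.28 = 8.8 points; 0.35/0.76 − 0.35 = 11.1 points.

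**5. What the rule permits.** Suppose the experimental protocol has lost all of the conservative benefit, so its true rate is the conventional-care rate at RR 0.85. By normal approximation with 92 per group, the probability of declaring non-inferiority is Φ[(0.10 − d)/SE − 1.96], where d is the true difference.

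- Control 28%, experimental 32.9%: d = 0.0494, SE = √[(0.28×0.72 + 0.329×0.671)/92] = 0.0678, so Φ(0.747 − 1.96) = 11%.
- Control 35%, experimental 41.2%: d = 0.0618, SE = √[(0.35×0.65 + 0.412×0.588)/92] = 0.0715, so Φ(0.535 − 1.96) = 8%.

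A margin no wider than the conservative benefit would hold this at 2.5% or less.

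**6. Power if the two-thirds rule were applied on the absolute scale.** 92 per group, 95% CI, and a true 7-point advantage for the experimental arm:

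- Control 28%, experimental 21%, margin 3.3 points: SE = 0.0632, (0.0329 + 0.07)/0.0632 = 1.63, Φ(1.63 − 1.96) = 37%.
- Control 35%, experimental 28%, margin 4.1 points: SE = 0.0683, (0.0412 + 0.07)/0.0683 = 1.63, again 37%.

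**The case against.** **A 10-point margin can be defended clinically.** It may be. The protocol, however, does not argue it on clinical grounds alone; it gives a numerical derivation, and that derivation is wrong. The objection is a good reason to keep the number and drop the derivation.

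**The margin does not exceed the PGDT benefit under every reading.** This stands. A reader might infer that 10 points is larger than the whole benefit of PGDT without qualification. The document's best estimate is RR 0.76; 0.85 is the unfavourable confidence limit. At RR 0.76 and a 35% control rate the benefit is 11.1 points, slightly above the margin. The unqualified statement fails there. It holds for the conservative effect, which is the basis the protocol chose, and for RR 0.76 with a 28% control rate.

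**The trial would not routinely pass a harmful protocol.** This also stands. It is tempting to say that a protocol 10 points worse could be accepted, but at a true 10-point excess the chance is about 2.5%. With 92 per group, an upper bound below 10 points requires the experimental arm to be observed about 3 to 4 points better. The excess error applies to complete loss of the conservative benefit and is 8 to 11%.

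**The protocol never promises to prove a preserved fraction of benefit.** Correct as to the decision rule and the stated aim. Persistence of the effect is an expectation offered as a reason for the design. The two-thirds statement nevertheless invites that interpretation of a positive result.

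**The control rate is ambiguous and no conventional-care rate is given.** True, so the implied margin is a range. No choice among the assumed rates brings it near 10 points.

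**Conclusion.** The concern holds in a limited form. The stated justification of the margin is false: a 10% relative reduction has been used as 10 absolute points. If 28–35% are PGDT rates, the stated rule gives 3.3 to 4.1 points (2.8 to 3.5 if they are conventional-care rates), and 10 points is 1.6 to 2.0 times the whole conservative benefit. Meeting the margin therefore cannot show that any of that benefit is kept. The chance of declaring non-inferiority when all of it is lost is about 8 to 11%, by normal approximation with 92 per group analysed.

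The result rests on RR 0.85 as the reference effect, as the protocol chose, and on complication rates near those assumed. The documents do not show that 10 points is unacceptable as a pragmatic margin.

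**What to change.** In Statistical analysis:

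1. Delete the statement that 10 points is two-thirds of the PGDT effect.
2. Keep the margin as 10 absolute percentage points and describe it as pragmatic.
3. Limit a positive conclusion to: not worse than the control protocol by more than 10 percentage points.
4. State that this does not show that the benefit of PGDT over conventional therapy is preserved.
5. Report the upper 95% confidence bound beside one reference value, the absolute equivalent of RR 0.85 at the observed control rate (about 5 to 6 points at 28–35%).

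The cost is wording and a weaker permitted claim; no extra patients are required.

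If the two-thirds rule is retained instead, state the margin on the absolute scale it implies and restate the power: about 37% at 92 per group with a 95% confidence interval, even with a true 7-point advantage. For a trial that Trial status describes as already recruiting, that is the far more expensive route.

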### General care and procedures

Patients undergoing elective non-cardiac surgery will be screened to participate to the study. They will be enrolled and allocated to one of the two groups if they meet all inclusion criteria and none of exclusion ones. All patients will be undergone to general anesthesia and mechanically ventilated with a tidal volume of 8 ml/kg and a positive end expiratory pressure (PEEP) of 5 cmH2O. FiO_2_ will be set at discretion of attending anesthesiologist to maintain normoxia. An arterial cannula will be used for continuous arterial monitoring. The arterial transducer will be zeroed at the level of the fourth intercostal space in the middle axillar line. The square-wave test will be used to assess the presence of over−/under-dumping on the arterial signal. A CO monitoring system will be used to record hemodynamic parameters. A central venous catheter will be placed after induction of anesthesia. A balanced crystalloid solution at the rate of 1 ml/kg/h will be administered intraoperatively. Any further fluid bolus will be administered according to the protocol in which the patient is allocated. Balanced crystalloid solutions are the only fluids permitted. Packed red blood cells will be transfused to maintain Hb ≥8 g/dl, at discretion of attending anesthesiologist. Mean arterial pressure will be maintained between 60 and 100 mmHg modulating anesthetic drugs on surgical stimulus or using vasopressor/vasodilator drugs, at discretion of attending anesthesiologist.

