### Protocol a

Patients allocated to protocol A will received a GDT protocol based on dynamic parameters of fluid-responsiveness for optimization of fluid status (Fig. 1). Dobutamine will be used with discretion of the attending anesthesiologist as clinically needed. The protocol will be continued postoperatively up to 6 h when dynamic parameters remain applicable (controlled mechanical ventilation, absence of arrythmia, etc.). On the other hand, fluid challenge technique with 250 ml of crystalloid over 5 min will be used for fluid optimization considering 10% increase in CO as positive response.

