## Discussion

The role of perioperative hemodynamic optimization has been clearly shown by literature and the current spreading of mini-invasive monitoring systems able to estimate CO permits an easier application of these protocols than occurring in the past when only invasive techniques (e.g. pulmonary artery catheter) were available. As a predefined target of CO or DO_2_ seems to be not adequate for every patient, a personalized therapy is likely more appropriate. Following this concept, dynamic parameters of fluid-responsiveness (PPV and SVV) allow to titrate fluid administration aiming an increase of CO as a consequence of preload optimization but avoiding fluid overload. This approach has the advantage of personalized fluid therapy, but it does not consider if CO is adequate or not because preload optimization occurs independently from parameters of tissue perfusion and oxygen consumption. A protocol based on O_2_ER considers this second important aspect. An O_2_ER higher than a predefined cutoff is reflecting an inadequate DO_2_ to tissue and consequently an inadequate CO. This condition, but not fluid-responsiveness per se, is the trigger to start hemodynamic optimization. Moreover, in this contest we believe that CVP may be useful to limit fluid administration independently from PPV or SVV value. In fact, CVP depends on several conditions including preload status but also on cardiac function and ventricular compliance. Thus, this trial aims to demonstrate that this latest strategy of perioperative hemodynamic optimization is not inferior to the former in term of postoperative complications, but it may be responsible for a lower fluid administration. We decided to conduct a non-inferiority study because PGDT is routinely applied in this kind of patients due to the demonstrated benefits on outcome. Thus, small difference in reduction of postoperative complication rate between two different PDGT protocols seems reasonable.

Methodologically, the main limitation of this trial is the inability to blindly administer the interventions. However, this point is not clinically resolvable in this research field. Moreover, if participation of several centers may increase enrollment rate and may potentially extend the applicability of results, on the other hands too few patients per center may increases heterogeneity.

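### Total fluid and fluid balance are compared by unadjusted t test or Mann–Whitney; a model with type of surgery and weight, reporting a difference in ml with 95% CI, would be a free improvement

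*Protocol article*

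**What the plan says.** All references are to the protocol article.

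- **Outcomes.** Objectives lists as secondary "the total amount of fluid administered, the total fluid balance, the needs of vasopressor/inotropes", followed by length of stay and 28-day mortality. The fluid outcomes are totals. No scale is given for drug need.
- **Tests.** Statistical analysis states that "Student t test or Mann–Whitney U test will be used to analyzed secondary outcomes as appropriate". Mortality has its own rule (Kaplan–Meier, log-rank, Cox). Fisher's exact and chi-square tests are named for the primary end point, and a 95% confidence interval is mentioned only there. Summaries are mean and SD, or median and interquartile range, according to a normality check.
- **Covariates.** The only adjusted model is the Cox regression set out with mortality. Type of surgery is among its candidate variables and weight is not. Data collection lists weight at randomisation.
- **Sources of spread in volume.** The inclusion criteria admit four kinds of surgery. Under General care and procedures, "A balanced crystalloid solution at the rate of 1 ml/kg/h will be administered intraoperatively" and "Any further fluid bolus will be administered according to the protocol in which the patient is allocated". The bolus rules are in figures that are not shown. The one bolus size in the text, under Protocol A, is a fixed volume: "fluid challenge technique with 250 ml of crystalloid over 5 min will be used for fluid optimization".
- **Role of the fluid outcome.** The Discussion says of the oxygen-extraction strategy that "it may be responsible for a lower fluid administration".

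**The concern.** A non-inferior result is easier to act on when the new strategy offers something in return. Lower fluid volume is one such return that the Discussion raises, so readers will want to know how many ml were saved and how precisely.

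Two features of the stated method work against that:

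1. Total volume is likely to differ between gastrointestinal, urologic, gynaecologic and vascular operations, and slightly with body weight. Neither depends on the allocated arm. An unadjusted comparison leaves this variation in the error term.
2. If the normality check leads to Mann–Whitney with medians and interquartile ranges, the stated output is a p value and two medians, without an adjusted difference in ml and its interval.

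A smaller matter is that the same sentence covers need for vasopressors or inotropes. If that item is yes/no, the natural report is a proportion per arm and a risk difference, which the plan does not name.

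**Working it through.** The document gives no SD, target difference or sample size for the fluid outcomes, so there is no planned figure to reproduce. The inputs it does give are 100 enrolled per arm (Sample size calculation) and the 1 ml/kg/h infusion. Everything marked *assumed* is not in the document.

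**1. What adjustment can give.** With a baseline covariate set explaining a share R² of the variance, the standard error is multiplied by √(1 − R²).

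With 100 per arm and no adjustment, the difference detectable with 80% power at two-sided 0.05 is (1.960 + 0.842) × √(2/100) = 0.396 SD. For that same difference:

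| R² (*assumed*) | SE multiplier | Interval narrower by | Power | Equivalent n per arm, 100/(1 − R²) |
|---|---|---|---|---|
| 0 | 1 | 0 | 80.0% | 100 |
| 0.10 | 0.949 | 5% | 84.0% | 111 |
| 0.20 | 0.894 | 11% | 87.9% | 125 |
| 0.30 | 0.837 | 16% | 91.8% | 143 |

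**2. Weight through the infusion alone.** R² = (1 ml/kg/h × hours × SD of weight / SD of total fluid)².

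- Central case (*assumed* 4 h, 15 kg, 800 ml): (60/800)² = 0.0056, so the SE falls by 0.3%.
- Largest case in the range tried (*assumed* 6 h, 20 kg, 500 ml): (120/500)² = 0.058, so the SE falls by 2.9%.
- Smallest case (*assumed* 2 h, 12 kg, 1200 ml): (24/1200)² = 0.0004, so the SE falls by 0.02%.

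Weight alone therefore buys little on the visible text.

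**3. Type of surgery.** As an illustration, *assume* four equally frequent types whose mean totals rise in steps of 250 ml, and a total SD of 800 ml. The between-type variance is 250² × (4² − 1)/12 = 78,125. Then R² = 78,125/640,000 = 0.12, and the SE falls by 1 − √0.878 = 6%. This shows that a gain of that order is plausible. It does not estimate the gain.

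**4. Whether to divide by weight instead.** A simulation was run with *assumed* mean weight 75 kg (SD 15), mean duration 4 h (SD 1.2) and a mean of four boluses.

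- Fixed 250 ml boluses: weight explains 1.3% of the variance, and dividing by weight raises the coefficient of variation from 0.39 to 0.44.
- Boluses per kg of similar mean volume: weight explains 20%, and dividing by weight lowers it from 0.44 to 0.39.

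Which case applies depends on figures that are not shown. Regression adjustment lets the data set the weight coefficient, so it does not depend on knowing which case applies.

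**5. Drug need, if yes/no.** With *assumed* counts of 30/100 and 45/100, the p values are 0.0285 (t), 0.0290 (Mann–Whitney) and 0.0285 (chi-square), so the choice of test hardly matters. The useful report is the risk difference: 15 points, SE = √(0.30 × 0.70/100 + 0.45 × 0.55/100) = 0.068, 95% CI about 1.7 to 28.3 points.

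**The case against.** The strongest reply is that nothing here is an error. Unadjusted t and Mann–Whitney comparisons of randomised arms are valid, the trial was not sized on fluid, and covariates for secondary outcomes are often settled in an analysis plan that is not shown. The validity point stands in full. On the last point, the article does not leave the method open: it names two tests, neither adjusted, and its wording allows a choice only between them. Improving a stated method is fair comment.

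A reader might also infer more than the document supports:

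- **That fluid is dosed by weight, so raw totals are the wrong scale.** Only the background infusion is shown to be per kg, and the one visible bolus is a fixed 250 ml. On that text, scaling to ml/kg could add variability.
- **That the infusion alone creates a large spread.** At 1 ml/kg/h it runs from 60 × 2 = 120 ml to 90 × 6 = 540 ml across *assumed* extremes, but duration contributes most of this. At 4 h, 60 against 90 kg differs by 120 ml; at 75 kg, 2 against 6 h differs by 300 ml. Duration is not in the proposed model.
- **That a substantial loss of power is demonstrated.** Any such figure rests on an assumed SD, difference and R².
- **That drug need is tested wrongly.** Its scale is undefined. The named tests can suit dose or duration, and a t test on a 0/1 item does yield the risk difference.
- **That lower fluid is the declared justification for the strategy.** The Discussion words it as a possibility and argues mainly that oxygen extraction reflects whether cardiac output is adequate.

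**Conclusion.** The point holds as a modest gain in efficiency and estimation, and should be labelled a free improvement. The stated tests are valid, but they forgo precision available from data already planned, and the rank-test route gives no adjusted difference with an interval for outcomes that readers will use to judge a possible benefit.

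The size is uncertain. Weight through the documented infusion is worth under about 3% of the standard error, and under 1% in the central case. A total R² of 10% to 30% would narrow the interval by 5% to 16%, but that range is assumed and any contribution from type of surgery cannot be derived from the document. For drug need, what remains is an ambiguity of scale.

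No bias is implied. The point is confined to secondary outcomes and has no effect on the primary non-inferiority test.

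**What to change.** Replace the single sentence on secondary tests with two rules.

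1. **Total fluid and total fluid balance:** a linear model with arm, type of surgery and baseline weight, using robust standard errors. Report the adjusted mean difference in ml with 95% CI. Keep Mann–Whitney as a sensitivity analysis. Do not make ml/kg the main analysis.
2. **Need for vasopressors or inotropes:** state the scale. If it is yes/no, report the proportion per arm and the risk difference with 95% CI, using the chi-square or Fisher test already named for the primary end point.

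The cost is wording in the analysis plan and slightly more analysis work, with the model fixed before the data are seen. Weight is already recorded and type of surgery is already a named model variable, so neither patient numbers nor data collection need change.
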